# The effects of royal jelly supplementation on oxidative stress, inflammatory mediators, mental health, cognitive function, quality of life, and clinical outcomes of patients with ischemic stroke: study protocol for a randomized controlled trial

**DOI:** 10.1186/s40795-023-00690-4

**Published:** 2023-02-16

**Keywords:** Royal jelly, Ischemic stroke, Quality of life, Inflammation, Integrative medicine

## Abstract

**Background:**

Stroke is a debilitating disease that affects over 15 million people worldwide each year, resulting in the death of one-third of those people and severe disability in two-thirds of survivors. Previous studies reported various health benefits of Royal jelly in the context of its anti-inflammatory properties. We will aim to investigate the effects of royal jelly supplementation on oxidative stress, inflammatory mediators, mental health, cognitive function, quality of life, and clinical outcomes of patients with ischemic stroke.

**Methods:**

The present study will be a triple-blind randomized placebo trial. Patients who meet our eligibility criteria will be assigned to the intervention or the control groups to receive allocated intervention for 12 weeks. Individuals of the intervention group will consume 1000 mg of Royal jelly dragee daily after breakfast. Subjects of the control group will receive a placebo dragee identical to the Royal jelly dragee. The severity of the stroke, cognitive function, mental health, quality of life, clinical outcomes, and biochemical measures will be assessed at baseline and post-intervention.

**Discussion:**

The current study is designed to investigate the effectiveness and safety of royal jelly supplementation in a randomized, parallel, two-arms, single-center, triple-blind, placebo-controlled manner. This study will provide evidence as a phase III clinical trial.

**Trial registration:**

IRCT20180818040827N4, registered on 16 October 2021. https://www.irct.ir/trial/59275.

## Background

### Background and rationale

Stroke is a debilitating disease that affects over 15 million people worldwide each year, resulting in the death of one-third of those people and severe disability in two-thirds of survivors. A stroke is a clinical syndrome that is defined as a sudden loss of focal or general brain function for more than 24 hours that can lead to death [1]. Nearly, 80% of strokes are ischemic. The incidence of stroke in men is 33% higher than in women, while the severity and rate of mortality and disability following stroke are higher in women than men [2].

One of the changes that occur at the cellular level is an increase in the inflammatory status. Inflammation of neurons following stroke is directly involved in the repair of damaged neurons and other pathologies of the disease [3]. Inflammation causes exacerbation of vascular dysfunction as well as the death of nerve cells, so the extent of inflammation is a key indicator in determining the prognosis in these patients, and controlling the inflammatory status after stroke is important in reducing secondary brain injuries [4]. Following an ischemic stroke, blood flow to certain parts of the brain is reduced, which in turn leads to a decrease in oxygen and glucose uptake by the brain cells [4]. Disruption of blood flow leads to the onset of inflammatory pathways and ultimately leads to the loss of cell antioxidant defenses and overproduction of reactive oxygen species (ROS). The resulting oxidative stress leads to neuronal dysfunction and death [5, 6]. It also plays an important role in the pathology of depression, mood disorders, cognitive function, and post-stroke fatigue [7–9]. The principal problem is a lack of specific pharmacological therapy for the wide range of post-stroke complications, while many attempts have been carried out so far [10]. Therefore, finding novel, safe, and inexpensive complementary therapies that encompass most of the post-stroke complications should be prioritized to manage this condition.

Royal jelly is known as a functional food that is produced by nurse bees to feed queen bees and young worker larvae. Its main constituents include water (60–70%), protein (9–18%), sugar (7–18%), and fat (3–8%) in addition it contains minor compounds such as minerals (Cu, Mn, Mg, Zn, K, Ca, Na, and Fe), amino acids (Trp, Lys, Phe, Met, Thr, Ile, Leu, Val), and vitamins (A, B complex, C and E) [11]. Previous studies reported various health benefits of Royal jelly including fertility, estrogenic, neuroprotective, hepato-renal protective, anti-hypertension, anti-hyperlipidemic, anti-diabetic, anti-cancer, immunomodulatory, anti-aging, wound healing, antioxidant, antimicrobial, and anti-inflammatory effects [12–14]. Administration of royal jelly in vitro inhibited the production of pro-inflammatory cytokines such as TNF-α and IL-1, − 6 in a dose-dependent manner [15]. Other in-vivo and in-vitro studies also proposed anti-inflammatory and anti-oxidant properties of royal jelly [16–19]. Royal jelly consumption by asymptomatic overweight adults demonstrated positive effects on antioxidant and inflammation capacity, and lipid profile [20]. Moreover, it provided a beneficial impact on fatigue and anorexia in patients with renal cell carcinoma [21]. Additionally, administration of 1000 mg/d royal jelly for 8 weeks in type 2 diabetes mellitus patients improved markers of oxidative stress and glycemia indices [22].

### Objectives

We will aim to investigate the effects of royal jelly supplementation on oxidative stress, inflammatory mediators, mental health, cognitive function, quality of life, stroke severity, appetite, and fatigue of patients with ischemic stroke.

### Study design

The present study will be a randomized, parallel, two-arms, single-center, triple-blind, placebo-controlled superiority clinical trial.

## Methods

### Setting

The current trial will be performed in Alzahra hospital which is an educational hospital affiliated with Isfahan University of Medical Sciences, Isfahan, Iran.

### Eligibility criteria

Inclusion criteria:Diagnosis of acute ischemic stroke by an expert neurologist ([name])National Institutes of Health Stroke Scale (NIHSS) score between 5 and 20Age between 45 and 80 years

Exclusion criteria:Ischemic stroke in the brain stemPrevious history of stroke or a history of stroke with a score of modified Rankin Scale (mRS) ≥ 1Adherence to any specific diet or using antioxidants or multivitamin supplements over 12 weeks before enrollment or during the studyPregnancy or lactationPatients with acute liver or kidney disease, cardiovascular disease, malignancies, and other neurological disordersPatients with asthma, dermatitis, and a history of allergyPatients with mental retardationPatients who are taking warfarinAllergy or hypersensitivity to honey or its by-productsAny unwanted side effects after taking a supplement or placeboRecurrence of stroke or deathCompliance of less than 80% to the intervention (consumption of less than 80% of Royal jelly supplements that should be taken during the 12 weeks of the intervention will be considered as low compliance)

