### Sample size

The sample size was calculated based on the primary outcome of the trial, the mRS. It was assumed that a total sample of 32 patients (32 patients per group), which includes a 10% dropout factor would provide 80% power to detect a difference in the mean of mRS between the royal jelly supplementation and placebo groups. Assuming means of 1.5 in the royal jelly supplementation group and 2.1 in the placebo group; a similar standard deviation (SD) of 0.8 between the two groups; and a two-sided test with a type I error of 0.05.

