### Baseline assessment

Eligible patients will be interviewed by a neurologist ([name]) and a nutritionist ([name]) to collect related information and complete questionnaires. Through a face-to-face interview, demographic variables of participants including age, sex, education, job, smoking, drug abuse, history of stroke in first-degree relatives, dysphagia, dysphasia, time since stroke, the affected area, co-existing disease, and medication will be gathered.

The NIHSS will be calculated for each participant at the baseline to evaluate the severity of ischemic stroke. The NIHSS is a reproducible, reliable, and valid instrument that examines 11 items including the level of consciousness, gaze, visual fields, facial palsy, motor arm and leg, ataxia, sensory, language, dysarthria, and extinction/inattention for a total score of 0–42 [23]. The score of 1–4, 5–15, 16–20, and 21–42 expressed mild, moderate, moderate to severe, and severe stroke, respectively [24].

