### Statistical methods

#### Statistical analysis for primary and secondary outcomes

All statistical analyses will be performed by Stata 17 (Stata Corp, College Station, TX, USA), according to the intention-to-treat (ITT) approach. We will use multiple imputations based on chained equations, which fill in missing values in multiple variables iteratively using a sequence of univariate imputation models with a fully conditional specification of prediction equations. Baseline characteristics and clinical features will be described by mean ± SD and absolute frequency (percentages) and compared between two intervention groups using the independent sample t-test for continuous data and a chi-square test for categorical data. Before statistical comparisons, all data were checked visually by a normal quantile-quantile plot (Q-Q plot) in combination with the Kolmogorov-Smirnov test for additional verification. Linear mixed-effects models will be fitted to assess changes from baseline within the treatment groups and differences of those changes between the groups concerning continuous outcomes over time. The magnitude of the effect will be presented as an adjusted mean difference and its 95% confidence interval. Also, a log-binomial regression model using robust standard error will be used to evaluate the risk of categorical outcomes between two intervention groups. The magnitude of the effect will be presented as an adjusted risk ratio (RR) and its 95% confidence interval. The independent variables included in the model are the treatment group and all potential confounders. Significance is defined as *P* < 0.01.

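### The exclusion criteria include conditions that can arise only after randomisation (low compliance, supplement use on study, side effects, recurrent stroke, death), which contradicts the stated intention-to-treat analysis

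*Protocol article*

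**What the plan says.** **Protocol article, Eligibility criteria.** One exclusion list mixes conditions present at entry with events that come later. The later items are:

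- following a specific diet, or taking antioxidants or multivitamins, while in the study (the same item also covers the 12 weeks before enrolment);
- any unwanted side effect after taking supplement or placebo;
- recurrent stroke or death;
- compliance under 80% with the intervention, explained as "consumption of less than 80% of Royal jelly supplements that should be taken during the 12 weeks of the intervention will be considered as low".

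**Protocol article, Statistical analysis for primary and secondary outcomes.** All analyses are to be done "according to the intention-to-treat (ITT) approach". The next sentence reads "We will use multiple imputations based on chained equations".

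**Protocol article, Sample size and Outcomes.** The primary outcome is fixed by "The sample size was calculated based on the primary outcome of the trial, the mRS". The severity-of-stroke outcome scores death as mRS 6.

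The article does not say whether a patient who meets one of the later criteria is still followed to week 12 or still counted in the analysis.

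**The concern.** An exclusion criterion decides who is in the trial. When it depends on what happens after allocation, membership can depend on treatment, on prognosis, or on both, and the groups compared are no longer the groups that were randomised. That is the situation ITT is meant to prevent, so the two sections cannot both be followed as written.

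A link with prognosis is plausible. Patients with NIHSS up to 20 are eligible. Dysphagia is recorded at baseline ("dysphagia, dysphasia, time since stroke") but is not an exclusion, and the product is one oral dragee a day. Patients who struggle to take it are likely to be the more disabled ones, with worse mRS, MMSE and quality of life. This is an inference; the documents give no data on it.

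The event items matter more. Recurrent stroke bears directly on the mRS, and death is its worst level. Excluding deaths removes part of the primary outcome scale.

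**Working it through.** **1. The plan's own figure.** Inputs from Sample size:

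- for the means, "Assuming means of 1.5 in the royal jelly supplementation group and 2.1 in the placebo group";
- for the spread, "a similar standard deviation (SD) of 0.8 between the two groups";
- for the error rate, "a two-sided test with a type I error of 0.05";
- 80% power and 10% dropout.

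The calculation is:

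- n per group = 2 × (1.960 + 0.842)² × 0.8² / 0.6² = 27.9, rounded up to 28.
- Allowing for dropout: 28 / 0.9 = 31.1, rounded up to 32 per group.

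The stated 32 per group reproduces. The planned difference, used as the yardstick below, is 2.1 − 1.5 = 0.6.

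**2. When the compliance rule can be failed.** Patients receive 28 dragees every 4 weeks, so 3 × 28 = 84 in all. Taking 68 of 84 is 81.0% and taking 67 of 84 is 79.8%, so a patient fails once 17 are missed. At one a day this could happen in week 3 or as late as week 12. In every case it is after randomisation.

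**3. The two sections side by side.**

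| Governing text | Consequence for a patient meeting a later criterion |
|---|---|
| Exclusion list | Leaves the trial; the analysed set is compliant, event-free completers, which is not ITT |
| ITT with multiple imputation | Stays in the analysis, but if follow-up stopped on exclusion, an outcome that could have been measured is replaced by a modelled one. Under the usual missing-at-random assumption the model draws mainly on patients who complied |

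For a death, the second reading would impute a value that is already known to be 6.

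**4. Possible shift in an arm mean with no treatment effect.** Assumption: k of 32 patients in one arm are removed, and their mRS averages g points above the rest of that arm. Removal lowers the arm mean by (k/32) × g. With g = 1:

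| k | Shift | Share of 0.6 |
|---|---|---|
| 2 | 0.0625 | 10% |
| 4 | 0.125 | 21% |
| 6 | 0.1875 | 31% |

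The effect on the between-arm difference is (k₁ − k₂)/32 × g when the removed patients are similar in both arms. If k₁ = k₂ it is zero. If the other arm loses half as many, the figures halve.

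Over a wider assumed range (10 to 30% removed, g from 0.5 to 1.5) the shift is 0.10 × 0.5 = 0.05 to 0.30 × 1.5 = 0.45 if one arm only is affected, and 0.025 to 0.225 if the other arm loses half as many.

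**5. One omitted death.** Assumption: the other 31 patients average the planned mean. Leaving out one death lowers the arm mean by (6 − 1.5)/32 = 0.14 in the royal jelly arm or (6 − 2.1)/32 = 0.12 in the placebo arm, which is 23% or 20% of 0.6.

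**6. Precision.** Under the planned assumptions, power is 85% with 32 analysed per group and 80% with 28. If exclusions went beyond the budgeted 10% (assumed rates), 20% leaves 25 per group and 75.5% power, and 30% leaves 22 per group and 70%.

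**The case against.** The strongest reply is that the article never says excluded patients' data leave the analysis. It states ITT and follows it at once with multiple imputation, so the exclusion list may be only a loosely placed list of withdrawal reasons. This stands in part. It means one cannot assert that ITT has been abandoned. It does not remove the contradiction, because imputing outcomes that could have been measured is a poor substitute for measuring them.

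A reader might infer three stronger things that the documents do not support.

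- **That the rule applies to one arm only**, because the explanation of low compliance names royal jelly. The criterion itself refers to the intervention, both groups are described as receiving an allocated intervention, and blinded staff could not apply a one-arm rule. This is careless wording, worth correcting but not evidence of a differential rule.
- **That the royal jelly arm will look better.** Stroke severity and dysphagia precede treatment and are expected equally in both arms under 1:1 randomisation. The dragees are described as identical in appearance and flavour, and both contain 53% honey powder. Nothing shows that removals would fall mainly in one arm, and balanced removals of similar patients give about zero shift.
- **That compliance is known only when the endpoints are measured.** Failure can be certain as early as week 3. Where it does become clear only at week 12, the outcome is probably available and can be used.

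**Conclusion.** The point holds as an internal contradiction that must be resolved before the analysis. Conditions that can arise only after randomisation are listed as exclusions while the analysis is declared to be ITT, and the article does not say which governs. Depending on the answer, the primary comparison is either one of compliant, event-free completers or one in which observable outcomes are replaced by imputed ones.

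The size and direction of any bias are unknown. The 10 to 31% of the planned difference rests on three assumptions: 2 to 6 removals of 32, a 1-point worse mRS in those removed, and nothing similar in the other arm. The documents support none of these directly, and the balanced case is about zero. The contradiction itself does not depend on them.

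**What to change.** Reconcile the two sections.

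- Limit the exclusion criteria to conditions present before randomisation.
- Move the later items to a separate list of conduct rules and recorded events. Keep the restriction on concomitant diet and supplements there instead of deleting it. State that meeting an item does not remove a patient from follow-up or from the ITT analysis.
- Collect week-12 outcomes for all randomised patients where possible, score deaths as mRS 6, and use imputation only for outcomes that are truly missing.
- Define compliance on the allocated dragees, royal jelly or placebo, and report it by arm. Use the 80% cut only in a labelled per-protocol sensitivity analysis.
- For any patient already removed under these rules, use the week-12 data where they exist, and report removals by arm and reason. The article does not say that anyone has been removed, but 43 patients had been included by 15 August 2022, and a missed week-12 visit cannot be made up later.

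The cost is an amendment, one sensitivity analysis and some effort to follow patients who stop taking the product or have an event. The effect estimate may also be diluted. If non-compliers get no benefit (assumption), 10% non-compliance reduces 0.6 to 0.6 × 0.9 = 0.54, which needs 35 per group before dropout. At 20% it is 0.6 × 0.8 = 0.48, which needs 44. Both compare with the planned 28. That dilution belongs to the effect an ITT analysis estimates; removing patients only hides it.

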### Ethics

Before the participants’ enrollment, an explanation will be provided to them by the researcher ([name]) regarding the informed consent contents, study procedures, objectives, and potential outcomes and their participation are voluntary. All enrolled patients will provide an informed written consent form. In cases where are unable to sign a consent form, his/her legal guardian writes informed consent. The protocol of the current study was approved by the Research Ethics Committee of Isfahan University of Medical Sciences (approval number: IR.MUI.RESEARCH.REC.1400.291; approval date: 9 October 2021) and also was registered at the Iranian Registry of Clinical Trials (registration number: IRCT20180818040827N4; registration date: 16 October 2021).

### Sample size

The sample size was calculated based on the primary outcome of the trial, the mRS. It was assumed that a total sample of 32 patients (32 patients per group), which includes a 10% dropout factor would provide 80% power to detect a difference in the mean of mRS between the royal jelly supplementation and placebo groups. Assuming means of 1.5 in the royal jelly supplementation group and 2.1 in the placebo group; a similar standard deviation (SD) of 0.8 between the two groups; and a two-sided test with a type I error of 0.05.

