## Trial status

The current study started for participant recruitment on November 9th, 2021. At the time of paper submission, recruitment is in progress and a total of 43 patients were included in the trial on August 15th, 2022.

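### The sample size sentence gives 32 both as the total and as the number per group; the protocol's own inputs support 32 per group, so 64 in total

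*Protocol article*

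**What the plan says.** The Sample size section sizes the trial on disability: "The sample size was calculated based on the primary outcome of the trial, the mRS". It then gives the size as "a total sample of 32 patients (32 patients per group), which includes a 10% dropout factor". The power claimed for that number is 80%, for a difference between the groups in mean mRS.

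The inputs follow in the same section. For the expected effect it writes "Assuming means of 1.5 in the royal jelly supplementation group and 2.1 in the placebo group". The spread is taken as equal in both arms, with an SD of 0.8, and the comparison is specified as "a two-sided test with a type I error of 0.05".

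Study design describes two parallel arms, and Randomization allocates patients 1:1. No other section states a total. Trial status reports that recruitment was still open and that "a total of 43 patients were included in the trial on August 15th, 2022". The Interim analyses section plans none.

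**The concern.** With two equal arms, a total of 32 and 32 per group differ by a factor of two, so one of them is wrong, and the article nowhere else says which is meant.

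The total tells the trial when enrolment is complete, and it tells readers, ethics reviewers and later meta-analysts whether the trial finished as planned. As printed, a reader cannot tell whether 43 included patients is 11 more than a target of 32 or about two-thirds of a target of 64 (43/64 = 67%). A trial that closed somewhere between 43 and 64 could cite the printed total as already met, although its power would be below the stated 80%.

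**Working it through.** **Inputs, all from the Sample size section unless noted**
- Difference in mean mRS: 2.1 − 1.5 = 0.6
- Common SD: 0.8, so the standardised difference is d = 0.6/0.8 = 0.75
- Two-sided alpha 0.05 (z = 1.960); power 80% (z = 0.842)
- Dropout 10%, already inside the stated number
- Allocation 1:1 (Randomization)
- 43 patients included, recruitment open (Trial status)

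**Step 1. Reproduce the plan's figure.** Normal formula for two means, per group:

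n = 2 × (1.960 + 0.842)² / 0.75² = 27.9, so 28 evaluable.

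Allowing for dropout: 28 / (1 − 0.10) = 31.1, so 32 per group and 2 × 32 = 64 in total. The per-group figure reproduces exactly.

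**Step 2. Try other conventions.**
- t-test instead of normal: 28.9, so 29 evaluable per group; 29/0.9 = 32.2, which is 33 if rounded up (66 in total).
- Multiplying by 1.1 instead of dividing by 0.9: 28 × 1.1 = 30.8, so 31 per group (62 in total).
- One-sided test, normal formula: 22 per group; 22/0.9 = 24.4, so 25 per group (50 in total).

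The two-sided variants fall between 62 and 66. None of the variants, including the one-sided one, gives a total of 32.

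**Step 3. Power at each size, two-sided alpha 0.05, d = 0.75.** The last two columns allow for 10% dropout.

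| Randomised | Per group | t-test power | Normal power | Per group left | t-test power | Normal power |
|---|---|---|---|---|---|---|
| 64 | 32 | 84.0% | 85.1% | 28.8 | 79.9% | 81.2% |
| 43 | 21.5 | 67.0% | 69.1% | 19.35 | 62.2% | 64.5% |
| 32 | 16 | 53.7% | 56.4% | 14.4 | 49.2% | 52.1% |

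The row for 43 takes the included patients as randomised and evenly split. Fractional group sizes are used as they stand.

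**Step 4. Set the result against conduct.** On 15 August 2022 the trial had 43 patients, 11 more than 32, and was still recruiting. That fits a target of 64 and does not fit a target of 32.

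**The case against.** The strongest reply is that this is a slip in one number which the article largely resolves itself. The parenthesis gives the per-group size, the inputs reproduce it, and enrolment had already passed 32. No input and no design choice is shown to be wrong. All of that stands. What remains is that a reader has to redo the calculation to learn the target, and that the wrong figure is the headline total for the primary outcome of a trial still recruiting.

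Three stronger readings are tempting, and the document does not support them.

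- *The trial could stop at 32 with about half the intended power.* Trial status rules this out: 43 patients were already in. The 54% and 49% describe what the printed total would have meant, not a risk still open. On the reported facts the lowest remaining stopping point is 43.
- *64 is the exact number required.* It is the right choice between the two printed readings. The strict minimum is 62 to 66, depending on formula and rounding, and by t-test 64 with 10% dropout gives 79.9%, which is 80% only after rounding.
- *64 secures 80% power for the analysis as planned.* The Sample size section ties its 80% to alpha 0.05, whereas the section on statistical analysis for primary and secondary outcomes sets significance at P < 0.01. At 0.01, 64 patients give about 63% by t-test, or 57% after dropout. That is a separate inconsistency. It neither causes nor cures this one.

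**Conclusion.** The point holds. The sentence contradicts itself, and the printed total of 32 is the wrong figure. It has to be corrected because a sample size statement must give one target, not because the trial is shown to be heading for half its power.

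In size, the total is understated by a factor of two. If enrolment closed at the 43 reported, power would be about 67%, or 62% after dropout, against 79.9% (t-test) to 81.2% (normal formula) for 64 after dropout.

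These figures rest on the protocol's own means, SD and dropout rate, on a two-sample comparison of means at two-sided alpha 0.05, and, for 43, on an even split between groups.

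**What to change.** In the Sample size section, change the total to 64 patients, keep 32 per group, and keep the statement that 10% dropout is included. Name 64 randomised as the recruitment target, and say that the 80% power applies at the two-sided alpha of 0.05 given there.

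If an evaluable number is added, it should be 28 per group, since 28/0.9 = 31.1 rounds up to 32. Writing 29 would not agree with 32: 29/0.9 = 32.2 rounds up to 33, and 32 × 0.9 = 28.8 falls short of 29.

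The cost is one corrected number and two clarifying phrases. The design, the per-group target and ongoing recruitment do not change. The conflict with the P < 0.01 threshold needs its own resolution and should not be folded into this correction.
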